## Interventions

### Genetic testing

Genotyping is planned for participants in groups 3 and 4 to support the calculation of of a commercially available genome-wide PRS, provided by an external provider. Genotyping will be performed using Illumina microarray technology (21), a cost-effective platform for large-scale SNP profiling in disease and population genetics studies. This approach generates data on millions of genetic variants per individual. Missing genotypes will be imputed using a modified version of the GLIMPSE algorithm (22), leveraging reference panels from the 1,000 Genomes Project (23) to ensure high-quality genome-wide coverage.

The PRS was developed and validated in large, ancestrally diverse cohorts (totaling over 29,000 individuals across multiple genetic ancestry groups, including European, African, South Asian, and others), demonstrating robust predictive performance (odds ratio per standard deviation of approximately 1.57) (24).

The resulting CVD genetic risk profile will be communicated to clinicians (and subsequently to participants) using a three-tier classification based on the participant's PRS percentile rank within the population distribution:

**Normal risk:** PRS below the 75th percentile.**Moderate risk:** PRS between the 75th and 97th percentiles (approximately 2-fold increased risk compared to the population average).**High risk:** PRS at or above the 97th percentile (top 3% of the population; approximately 3-fold increased risk compared to the population average).

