### Trial population and setting

The population will be composed of 120 participants aged 40 to 69 years with a diagnosis of metabolic syndrome and a 10-year CVD risk between 2.5 and 10%, who are under the care of GPs in Rome metropolitan area 2025–2026 (Italy).

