#### T1 (1 month post-enrolment)

All participants will be informed about their lifestyle profile through direct communication, including telephone contact, and will receive written materials via email outlining standard behavioral interventions to reduce cardiovascular risk, regardless of group assignment. Participants in groups 3 and 4 will receive detailed explanations of their genetic risk results derived from the PRS analysis. This will include information about their categorized risk level and the implications for their cardiovascular health, helping them understand how their genetic predisposition may affect their overall risk.

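### The PRS tier multiples (about 2-fold and 3-fold), their population-average comparator and the odds ratio of 1.57 per SD do not fit together; the moderate tier is the clear discrepancy

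*Protocol article*

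**What the plan says.** The Genetic testing section of the protocol article summarises the commercial PRS by an "odds ratio per standard deviation of approximately 1.57", with a literature citation. It then sets three tiers by "PRS percentile rank within the population distribution":

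- normal: "PRS below the 75th percentile", with no multiple given;
- moderate: "PRS between the 75th and 97th percentiles (approximately 2-fold increased risk compared to the population average";
- high: the "top 3% of the population; approximately 3-fold increased risk compared to the population average".

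The two multiples carry no citation of their own, and their derivation is not described. The section says that the profile goes to clinicians, and then to participants, in the form of these three tiers. Under T1, participants in groups 3 and 4 are to receive "information about their categorized risk level and the implications for their cardiovascular health".

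**The concern.** An odds ratio per SD and a set of percentile cut-points together largely determine the average risk in each tier. A score with 1.57 per SD has a modest gradient. A band that starts at the 75th percentile should therefore not average twice the population risk. Either the multiples, the comparator or the odds ratio needs correcting.

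The multiples describe the meaning of the tiers that the PRS arms will be told about. Risk perception and the perceived benefits of the PRS are among the things the study measures. If the multiples enter the T1 explanation with the wrong comparator, participants in an elevated tier could be told that their risk is higher than the score supports, and their answers would partly reflect that.

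**Working it through.** **Inputs from the article:** odds ratio 1.57 per SD; cut-points at the 75th and 97th percentiles; stated multiples 2 and 3 against the population average.

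**Assumptions (not stated in the article):** the score Z is standard normal, risk is proportional to exp(bZ), and the odds ratio is close to a risk ratio. The last assumption is relaxed in step 4.

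**Step 1: constants.** b = ln(1.57) = 0.451; z(0.75) = 0.674; z(0.97) = 1.881. Then Φ(0.674 − 0.451) = Φ(0.223) = 0.588 and Φ(1.881 − 0.451) = Φ(1.430) = 0.924.

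**Step 2: try to reproduce the stated figures with the stated comparator.** Mean risk in a tier divided by mean population risk is [Φ(u − b) − Φ(l − b)] / [Φ(u) − Φ(l)], where l and u are the tier limits.

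- Below the 75th: 0.5884 / 0.75 = 0.785
- 75th to 97th: (0.9236 − 0.5884) / 0.22 = 1.52
- Top 3%: (1 − 0.9236) / 0.03 = 2.55

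The weighted sum 0.75 × 0.785 + 0.22 × 1.524 + 0.03 × 2.547 is 1.00, as it must be. The stated 2 and 3 are not reproduced. They exceed the results by 31% (2 / 1.524) and 18% (3 / 2.547). For the moderate tier the excess risk is 100% as stated and 52% as computed.

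**Step 3: other comparators.** Mean population risk is exp(b²/2) = 1.107 times the risk of a person with Z = 0. Multiplying by 1.107 gives the figures against an average score; dividing by 0.785 gives those against the normal tier.

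| Comparator | Moderate | High |
|---|---|---|
| Stated in the article | about 2 | about 3 |
| Mean population risk | 1.52 | 2.55 |
| Person with an average score (Z = 0) | 1.69 | 2.82 |
| People below the 75th percentile | 1.94 | 3.25 |

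Only the last row comes near both stated figures.

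**Step 4: sensitivity.**

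- Rounding of the odds ratio (1.565 to 1.574) gives 1.52 to 1.53 and 2.53 to 2.56 against the mean.
- A logistic model on the risk scale, at average risks of 2.5%, 5% and 10%, gives 1.51 / 2.46, 1.50 / 2.38 and 1.47 / 2.23 against the mean. I borrowed this range from the eligibility criterion only to convert odds to risk. The gap widens.
- Against the mean, a 3-fold top tier needs about 1.72 per SD, and the moderate tier is then 1.62. A 2-fold moderate tier needs about 2.76 per SD, and the top 3% is then about 6.4-fold. Under this model no single odds ratio gives both figures.

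**Step 5: a check without normality.** Tier risks relative to the mean must average to 1. If 22% of people have 2 and 3% have 3, they contribute 0.22 × 2 + 0.03 × 3 = 0.53, and the other 75% average (1 − 0.53) / 0.75 = 0.63. The elevated tiers would then be 2 / 0.627 = 3.2 and 3 / 0.627 = 4.8 times the normal tier. That is much steeper than the 1.94 and 3.25 implied by 1.57 per SD.

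**Step 6: how many people.** With 120 participants in four equal arms, 60 are genotyped. If they follow the population distribution, 0.22 × 60 ≈ 13 are in the moderate tier and 0.03 × 60 ≈ 2 in the high tier.

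**The case against.** The strongest reply is that the comparator can be read in two ways and that every figure is given as approximate. If average means a person with an average score, the odds ratio gives 1.69 and 2.82. The high tier is then fairly about 3-fold, and the stated figures exceed the computed ones by only 19% and 6%. This stands for the high tier. It does not rescue the moderate tier, because 1.69 is a loose match to 2 even on the more favourable reading.

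A second reply is that the multiples may be empirical estimates from the provider, perhaps from a different cohort from the one behind the 1.57, and that neither normality nor log-linearity is stated. This also stands. The article shows that the figures do not fit together, but not which one is wrong.

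A reader might infer that participants will be told an overstated risk. The article does not go that far. It commits to conveying the tier and its implications, and it does not say that the multiple appears in the report or in the conversation. Nor can one infer that anyone would be placed in the wrong tier, because assignment is by percentile alone.

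Finally, the count of about 13 assumes that people selected for metabolic syndrome and a SCORE2 range have the population distribution of the score, which need not be so.

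**Conclusion.** The inconsistency is real. With a normal score and log-linear risk, 1.57 per SD supports about 1.5-fold and 2.5-fold against mean population risk (about 1.7 and 2.8 against an average-score person), not 2-fold and 3-fold. The moderate tier is the firm case and the high tier is borderline. Because 1.94 and 3.25 arise against the normal tier, a mislabelled comparator is the most likely explanation, but this cannot be settled from the article.

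The consequence is conditional: overstated risk could reach groups 3 and 4 if the multiples are used at T1. The figures enter no endpoint, model, sample-size argument or progression criterion. I therefore rate this as something that should be fixed, short of a critical fault.

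**What to change.** Before any PRS result is released, check the two multiples, their comparator and the odds ratio against the provider's validation data, and cite the source of the multiples. Then do one of the following:

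- keep the multiples and change the comparator to people below the 75th percentile, if the data confirm that reading; or
- keep the population average, say whether it means mean risk or an average score, and restate the multiples from those data. If only the odds ratio of 1.57 is available, they are about 1.5 and 2.5 against mean risk, with the normality and log-linearity assumptions stated.

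Use the same wording in any report or script for GPs and participants. The cost is a few words in the protocol and in the communication material, plus one query to the provider. Nothing in the design or analysis changes. With the second option the figures look less striking.

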### Wearable devices

Participants assigned to groups 2 and 4 will receive a short written user guide and will be instructed to use a wearable device in combination with a paired smartphoneapplication (25). The app is available for both Android and iOS devices and requires installation on a compatible smartphone, creation of a personal account and Bluetooth pairing with the wearable. The app provides consumer-facing health and activity indicators, including step count, sleep, heart rate, blood oxygen saturation, calories burned, and stress level, and also supports exercise session tracking. Additional technical characteristics relevant to study implementation are reported in Annex 2, Supplementary Table 1.

Use of the wearable device will not be actively monitored by the study team, and no data will be collected to assess adherence to device use.

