### Secondary endpoints

Lifestyle changes measured through the LF8 questionnaire (18), changes in cardiovascular risk profiles evaluated through SCORE2 (15), biochemical variations including glucose, total cholesterol, HDL cholesterol, LDL cholesterol, triglycerides and glycated hemoglobin (HbA1c).

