#### Enrolment (T0)

GPs will provide verbal and written informed consent to eligible individuals, including specific modules for genetic analysis. Then, participants will be formally enrolled and randomly assigned to one of the four study arms using a computer-generated randomization procedure implemented through the REDCap (Research Electronic Data Capture) system, which will also record all participants information during the study. The assignment to the intervention will not be blinded. Participants, research staff, and the medical team will become aware of study group allocation only after completion of the randomization procedures. Given the nature of the intervention, blinding of participants and healthcare professionals is not feasible, as participants will know whether they receive PRS information and/or access to the app and wearable device. Outcome assessment cannot be fully blinded, particularly for self-reported behavioral outcomes, because these outcomes are directly provided by participants who are aware of their allocation. Standardized study materials and instructions will be provided to GPs to support consistency in intervention delivery across study arms.

All participants will undergo a comprehensive assessment and cardiovascular evaluation. This will include the completion of questionnaires covering socioeconomic status, area of residence and key lifestyle factors such as smoking, alcohol consumption, dietary patterns, sleep and physical activity. Cardiovascular health will be assessed using the Life's Essential 8 (LE8) framework (18) developed by the American Heart Association (AHA), which encompasses eight domains: physical activity, nicotine exposure, sleep health, body mass index, blood lipids, blood glucose, blood pressure and diet (Annex 1, section 1, section 2, section 3). Each component is scored on a continuous scale from 0 to 100 according to AHA criteria. The overall LE8 score is calculated as the unweighted mean of the eight components, resulting in a composite score ranging from 0 to 100, with higher values indicating more favorable cardiovascular health. In line with AHA classification, scores will be categorized as poor (0–49), intermediate (50–79), or ideal (80–100). Dietary quality will be assessed using the modified Mediterranean Eating Pattern for Americans (MEPA) (19). Based on the LE8 assessment, participants will be categorized into favorable, intermediate, or unfavorable lifestyle profiles.

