Additionally, participants will be asked questions to assess their perceptions of cardiovascular risk and the perceived benefits of preventive interventions (20). All questionnaires are provided in Appendix 1.

For participants assigned to groups 3 and 4, saliva samples will be also collected to conduct PRS analysis to evaluate their genetic risk profile for CVD.

For participants in groups 2 and 4, wearable devices will be provided along with instructions on how to set up and use the accompanying mobile application.

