#### T2 (6 months post-enrolment)

All participants will be contacted by GPs by telephone for a follow-up assessment where they will complete the questionnaire to monitor changes in their health behaviors. Participants will be extemporarily informed of their progress and any updated lifestyle classification. Moreover, extra counseling and support will be provided to reinforce positive lifestyle changes.

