Despite these strengths, several limitations should be considered when interpreting the findings. First, the lack of blinding is inherent to the nature of the intervention. Participants, healthcare professionals, and research staff cannot be blinded to group allocation, and outcome assessment cannot be fully blinded, particularly for self-reported behavioral outcomes. Consequently, lifestyle-related outcomes such as diet, physical activity, smoking, alcohol consumption, and sleep habits may be affected by reporting, social desirability, or performance bias. To mitigate these risks, standardized questionnaires and data collection procedures will be used across all study arms, and objective clinical, anthropometric, and laboratory measures will be collected where applicable to complement self-reported outcomes. Blinding during data analysis will also not be feasible due to the collection of arm-specific variables; therefore, analyses will be conducted using coded participant identifiers and predefined statistical analysis procedures to reduce the risk of analytical bias. Wearable-generated data and app-level usage logs will not be directly collected for research purposes, and adherence will therefore be assessed through participant self-report, which may be subject to recall bias and inaccurate reporting. However, the wearable is intended primarily as a supportive tool to promote behavioral change rather than as a primary outcome measure. In addition, participants are nested within general practitioners, and although standardized materials are used to support consistent intervention delivery, some degree of clustering and potential contamination across study arms cannot be excluded. The study does not include a prospective economic evaluation or systematic assessment of implementation costs, limiting conclusions regarding cost-effectiveness and scalability. Finally, the qualitative component is based on voluntary participation, which may introduce self-selection bias, with more motivated individuals potentially over-represented.

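### Activity and sleep are self-reported in all arms, but only groups 2 and 4 get a device that displays them, so the exploratory wearable contrast on LE8 may mix behaviour change with device-informed reporting

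*Protocol article*

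**What the plan says.** **The endpoint.** Secondary endpoints lists "Lifestyle changes measured through the LF8 questionnaire". Enrolment (T0) calls the instrument LE8 and cites the same reference, so I read the two labels as one instrument. Its score "which encompasses eight domains: physical activity, nicotine exposure, sleep health, body mass index, blood lipids, blood glucose, blood pressure and diet". Each component runs from 0 to 100, and "The overall LE8 score is calculated as the unweighted mean of the eight components".

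**How activity and sleep are obtained.** Baseline assessment of all participants includes "completion of questionnaires covering socioeconomic status, area of residence and key lifestyle factors such as smoking, alcohol consumption, dietary patterns, sleep and physical activity". At T2 participants are telephoned, and "they will complete the questionnaire to monitor changes in their health behaviors". At T3 they complete a final lifestyle questionnaire in person. No other measure of activity or sleep is described.

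**Who sees readings of them.** Enrolment (T0) states: "For participants in groups 2 and 4, wearable devices will be provided along with instructions". The Wearable devices section says of the app: "The app provides consumer-facing health and activity indicators, including step count, sleep, heart rate, blood oxygen saturation, calories burned, and stress level", and adds exercise-session tracking. Data collection and management states that no wearable data are collected directly.

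**What the protocol says about bias.** The limitations paragraph of the Discussion accepts that "lifestyle-related outcomes such as diet, physical activity, smoking, alcohol consumption, and sleep habits may be affected by reporting, social desirability, or performance bias". Its answer is to use standardized questionnaires and procedures in all arms, supplemented where applicable by objective clinical, anthropometric and laboratory measures. Statistical analysis compares each intervention group with control in mixed models with group, time and their interaction, adjusted for baseline.

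**The concern.** Two things the wearable arms are later asked to report, activity and sleep, are things their device displays to them. The questionnaire is the same in all arms, but the information behind the answer need not be. At T0, before the device has been used, answers rest mainly on recall everywhere. At T2 and T3, groups 2 and 4 can consult or remember app readings, and groups 1 and 3 have no trial device to consult.

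Randomisation does not protect against this, because the intervention itself changes what informs the answer. A difference between arms 2 or 4 and control on LE8, or on its activity and sleep components, could then reflect changed behaviour, changed reporting, or both. At stake is the interpretation of an exploratory estimate that the protocol says will be read for its magnitude and precision.

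**Working it through.** The protocol states no effect size, SD or power for LE8, so there is no figure to reproduce. The check has three parts.

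**1. Do the planned safeguards reach the mechanism?**

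| Safeguard | Where | Effect on device-informed reporting |
|---|---|---|
| Same questionnaires in all arms | Discussion, limitations | Equalises the questions, not the information behind the answers |
| Objective clinical, anthropometric and laboratory measures | Discussion, limitations | Cover lipids, glucose, BMI and blood pressure; none covers activity or sleep |
| Baseline adjustment | Statistical analysis | The shift arises after T0 and only in groups 2 and 4, so it enters the group-by-time term |
| Wearable data as a check | Data collection and management | Not collected |

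None removes it.

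**2. How much of the score is exposed?** Inputs from Enrolment (T0): 8 components, equal weights, 2 exposed.

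- Share of the score: 2/8 = 25%.
- If reporting alone shifts activity by a and sleep by s, LE8 moves by (a + s)/8. With a = s = d this is 2d/8 = d/4. If a = −s the shifts cancel.
- The full-score contrast equals 0.75 × (contrast on the mean of the other six) + 0.25 × (contrast on the mean of activity and sleep). The two parts can therefore be reported separately.
- T2 is by telephone, with no blood tests or physical measurements described. On the mean of the four behaviour components (activity, sleep, diet, nicotine), the shift is 2d/4 = d/2.

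| Assumed d on both components | Shift in LE8 (d/4) | Shift in behaviour mean (d/2) |
|---|---|---|
| 5 | 1.25 | 2.5 |
| 10 | 2.5 | 5 |
| 15 | 3.75 | 7.5 |
| 20 | 5.0 | 10 |

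**3. How does that compare with the trial's precision?** 120 participants at 1:1:1:1 give 120/4 = 30 per arm. The SD of LE8 is not given, so I assume 8 to 12. This simple two-group calculation ignores attrition, clustering and any gain from baseline adjustment.

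- SE = SD × √(2/30). For SD = 10: 10 × 0.2582 = 2.58.
- Half-width of the 95% CI = 1.96 × SE: 4.05, 5.06 and 6.07 points for SD 8, 10 and 12.
- With no behaviour change and a composite shift Δ, the chance that the CI excludes zero is Φ(Δ/SE − 1.96) + Φ(−Δ/SE − 1.96).
- SD = 10, Δ = 2.5: Φ(−0.99) + Φ(−2.93) ≈ 0.16.
- SD = 10, Δ = 5.0: Φ(−0.02) + Φ(−3.90) ≈ 0.49.
- Over SD 12 to 8: 13% to 23% for Δ = 2.5, and 37% to 68% for Δ = 5.0, against 5% with no shift.

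An assumed shift of 20 points on both components would thus be about as large as the half-width. An assumed 10 points would be about half of it.

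**The case against.** **The bias is already disclosed.** The protocol says self-reported outcomes cannot be blinded and names activity and sleep among those open to reporting bias. This stands, and it lowers the severity. What is not disclosed is that the device can itself inform the answers in two of four arms, and the stated mitigation does not address that.

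**Nobody knows who answers from what.** A reader might infer that half the trial answers from device readings and half from recall. The documents do not support that. The exclusion criteria do not bar people who own a wearable, use of the trial device is not monitored, and the Discussion itself cites device discontinuation. Each would dilute the difference. The concern is therefore about what may happen, and the protocol plans no item that would show whether it did.

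**Annex 1 is not shown.** The wording and recall periods of the lifestyle items cannot be checked, and an instruction about devices may be there. This stands as a limit on confidence. The mechanism rests on the main text, which describes the mitigation in full without mentioning it.

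**The sizes are assumed.** The 10- and 20-point shifts have no source in the documents, and equal shifts in the same direction are the case with the largest effect for a given d. This stands: the figures show sensitivity and are not a forecast.

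**The consequence is limited.** A reader might infer that a wrong LE8 effect would be carried into the size of the definitive trial. No section says so. The progression criteria are recruitment, completeness of outcome data and GP willingness. Where the Discussion says exploratory data can inform later trials, its examples are cardiovascular risk profiles and lipid levels.

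**Conclusion.** The point holds as a minor one. Activity and sleep, 25% of LE8, are self-reported in all arms, while a trial device displaying them is given only to groups 2 and 4. Neither the common questionnaire nor baseline adjustment removes a resulting difference in reporting, so the exploratory wearable contrast on LE8 may combine behaviour change with a change in information source.

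Its size is d/4 composite points for an assumed reporting shift d on both components. The direction is open: readings could correct over-reporting and hide a real benefit, or correct under-reporting and suggest one that is absent. A reader might infer that the trial will show a false wearable effect; the documents support only that it could, in either direction.

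The conclusion assumes that T0 answers precede device use, that some participants in groups 2 and 4 draw on readings at follow-up, and that fewer do so in groups 1 and 3. The primary feasibility indicators and laboratory endpoints are not directly affected, and no activity or sleep input to SCORE2 is stated.

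**What to change.** 1. **Add one item at T2 and T3, in all arms**, asking whether a device or app reading, trial-issued or the participant's own, was used to answer the activity and sleep questions. This shows how far the information source differs between arms and captures devices owned by controls.
2. **For contrasts of groups 2 and 4 with control, report the activity and sleep components separately.** At T3, also give a prespecified sensitivity LE8 without them (mean of the remaining six) beside the full LE8. At T2 such a score would rest mainly on diet and nicotine, so the separate components are enough there.
3. **Name device-informed reporting in the limitations paragraph**, and state that a wearable effect confined to activity and sleep cannot be separated from a change in reporting.

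Two other measures may suggest themselves but are not recommended. Asking participants to answer from recall alone would not restore comparability, since after 6 to 12 months of feedback recall is itself informed by the device. Ruling out any claim based on activity and sleep would also discard a genuine effect on behaviours the device is meant to influence.

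The cost is one questionnaire item, one derived score from data already collected and a sentence or two of text. The six-component score cannot show a true effect on activity or sleep, so it supplements the full LE8 and does not replace it.
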